**Introduction**

Pain is the most common cause for physician consultation. It is the main symptom in many medical and dental conditions and can significantly alter the person's quality of life and general functioning. Endodontic post-treatment pain remains to be significant problem facing the dental profession. The presence of microorganisms as a result of failure to properly disinfect the canal is the most common cause of pain. Thus, endodontic therapy is primarily focused on maximum elimination of these bacteria. Antibacterial intra-canal dressing is advocated to eliminate remaining bacteria after chemo-mechanical preparation.

Calcium hydroxide, the most commonly used intra-canal medication is considered as the most favorable anti-microbial agent (Ghoddusi et al, 2006). It has been proven to be effective against endotoxins as demonstrated by *in-vitro* (Maekawa et al 2011) and *in-vivo* studies (Silva et al 2002). Calcium hydroxide also alters bacterial cell wall and denatures a potent endotoxin, lipopolysaccharide, thereby rendering it less antigenic (Walton et al, 2003).

Lipopolysaccharide (LPS), generally referred to as endotoxins, is one of the most important virulent factors participating in the development and maintenance of apical periodontitis (Pitts et al 1982) (Xavier et al 2013). Lipopolysaccharide is the major constituent of the outer cell wall of gram negative bacteria, which is released during disintegration, multiplication or death of the bacteria (Nair 2004). Clinical investigations have revealed the presence of endotoxins in 100% of the root canal samples in primary and secondary infectious diseases showing apical periodontitis, with high levels related to the development of clinical symptoms (Martinho & Gomes 2008). Because of the high toxicity of endotoxins *in-vivo* and *in-vitro*, even at a very low concentration, its neutralization/removal during endodontic treatment seems to be important for the healing process of the periapical tissues of infected root canals.

Even though calcium hydroxide is one of the most widely used intra-canal medicament due to its anti-microbial properties, there is no clear evidence of its effect on the post-treatment pain after the chemo-mechanical root canal preparation (Anjaneyulu et al, 2014). Other studies found that, Calcium hydroxide was not very effective in reducing post-treatment pain when it was used alone (Ehrmann et al, 2003) (Singh et al, 2013).

Antibiotic paste, is a mixture of metronidazole and ciprofloxacin, which is used as intra-canal medication for disinfection of necrotic teeth. Antibiotic paste has been reported to be effective at reducing bacterial numbers in the root canal systems of infected teeth (Mohammadi & Abbott 2009). When most commonly used medicaments fail in eliminating the symptoms, then antibiotic paste could be used clinically in the treatment of teeth with large periradicular lesions (Taneja & Kumari 2012).

Objectives of the present study: To test the null hypothesis whether the use of antibiotic paste will be more effective in reduction of pain and endotoxins than calcium hydroxide, or will these paste have disadvantages and complains more than the traditional method if used.

# Trial Design:

# Type: Parallel randomized clinical trial

# Allocation ratio: 1:1

# Framework: Superiority

# Aim of the Study:

To assess the ability of antibiotic paste versus calcium hydroxide used as intra-canal medication in reducing pain and level of endotoxins in necrotic teeth with apical periodontitis.

- **PICO approach**

**P:** **population**, patients with non-vital permanent teeth with apical periodontitis.

**I: intervention,** antibiotic paste intra-canal medication.

**C: control,** calcium hydroxide intra-canal medication.

**O: outcomes:**

|  | **Outcome measure** | **Tool for measurement** | **Unit of measurement** |
| --- | --- | --- | --- |
| Primary | Postoperative Pain | Numerical rating scale (Brunelli et al, 2010) | Ordinal |
| Secondary | Quantification of endotoxins | LAL assay | EU/mL |

Postoperative pain will be measured using Numerical Rating Scale (NRS) after 6, 12, 24 and 48 hours from the end of root canal obturation **(Evaristo et al. 2013)**

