A 2-stage access cavity preparation will be performed. The first stage involved the removal of caries without exposure of the pulp chamber by using a high-speed diamond bur. In the second stage, before entering the pulp chamber, the access cavity will be disinfected according to the decontamination protocol described previously. A new bur will be used to access the canal.

1. 1^st^ sample:-

The first endotoxin sample will be taken by introducing the paper points^[[2]](#footnote-2)^ into the full length of the canal (determined by radiographs and apex locator^[[3]](#footnote-3)^) and retaining them in position for 60 seconds. Next, the paper points will be placed in a glass tube and stored at -80^0^C for the LAL assay.

1. Preparation:-

-The root canals will be prepared with Gates-Glidden drills^[[4]](#footnote-4)^ sizes 4, 3 and 2 for the coronal part, and rotary Irace instruments^[[5]](#footnote-5)^ using an endodontic motor^[[6]](#footnote-6)^ with adjusted torque and speed according to the manufacturer's instructions. The rotary files will be introduced inside the canal using EDTA gel^[[7]](#footnote-7)^.

-Before the use of each instrument, irrigation with a syringe (27-G needle) Containing 3ml 2.5% sodium hypochlorite^[[8]](#footnote-8)^.

- Subsequently, 5% sodium thiosulfate will be used to inactivate NaOCl. Then, 5ml saline solution to wash the canal.

1. 2^nd^ sample:-

The second endotoxin sample will be taken as previously described just after the irrigation with saline solution.

1. Intracanal medication:-

The canals will be dried with paper points and filled with intracanal medication plugged into the canal by using Lentulo spiral^[[9]](#footnote-9)^ . The access cavities will be properly filled with Cavit^[[10]](#footnote-10)^.

- **Control group:** Ca (OH)_2_ Paste.
- **Experimental group:** antibiotic paste (ciprofloxacin, metronidazole)

1. The patient will be instructed to record his/her pain level on the pain scale chart after 6 h, 12 h, 24 h and 48 h.
2. 3^rd^ sample:-

After 7 days of intracanal medication, the canal will be accessed under rubber dam isolation by using the protocol for disinfection described previously. The medication will be removed, the final endotoxin sample will be taken just after the irrigation with saline solution.

1. Obturation:-

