# 0 reading represents “no pain”

# 3 readings represent “mild pain”

# 4- 6 readings represent “moderate pain”

# 7- 10 readings represent “severe pain”

- **Secondary Outcomes:**

The quantitative limulus amoebocyte lysate (LAL) test was used to measure endotoxin concentrations in the root canals by a commercial standard kit. The LAL assay is highly sensitive for detection of minute concentrations of endotoxin. LAL is an aqueous extract of blood cells (amoebocytes) from the horseshoe crab, Limulus polyphemus, that reacts with bacterial endotoxin or LPS. This reaction is the basis of the LAL test, which is used for the detection and quantification of bacterial endotoxins.

- **Participant timeline:**

1. Patients will be selected from the clinic of endodontic after eligibility.
2. They will be randomized and pretreatment diagnosed and radiographed at the same visit of treatment.
3. Patients will be treated in two visits and will record preoperative and postoperative degree of pain at 6, 12, 24 and 48hrs.
4. Patients will return pain charts to the operator on the second visit.

| **periods** | **Recruitment** | **Diagnosis** | **Periapical radiograph** | **Randomization** | **Follow up for postoperative pain** |
| --- | --- | --- | --- | --- | --- |
| Zero |  |  |  |  |  |
| 6 h |  |  |  |  |  |
| 12 h |  |  |  |  |  |
| 24 h |  |  |  |  |  |
| 48 h & close out |  |  |  |  |  |

- **Sample Size:**

The aim of this study is to compare the ability of antibiotic paste versus calcium hydroxide used as intra-canal medication in reducing pain and level of endotoxins in necrotic teeth with apical periodontitis. Based on previous study by Ehrmann, et al. (2003), a medium effect size of approximately 0.25 is expected. A total sample size of 24 patients will be sufficient to detect an effect size of 0.25, a power of 80%, and a significance level of 5%. This number has been increased to a total sample size of 28, to adjust for using nonparametric tests. The number is again increased to a total sample size of 36 (18 in each of the two groups) to allow for losses of around 25%. Sample size was calculated using G*Power program (University of Düsseldorf, Düsseldorf, Germany)^[[13]](#footnote-13)^ . minimal clinical difference 3.5 and 4.5 at 24 hrs and 48 hrs respectively.

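### The primary pain outcome is timed from obturation, but the step order and the chart-return rule collect it about a week earlier, before obturation

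*Protocol*

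**What the plan says.** The outcome table in the PICO section of the Protocol names the primary outcome "Postoperative Pain". The sentence under the table says it is measured "after 6, 12, 24 and 48 hours from the end of root canal obturation". This is the only sentence in the Protocol that gives the pain readings a starting event.

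The list headed Sequence of Procedural steps runs in this order: preoperative pain score, anaesthesia, access, first sample, preparation, second sample, medication and temporary filling. At that point the patient is "instructed to record his/her pain level on the pain scale chart after 6 h, 12 h, 24 h and 48 h". The next step is the third sample: "After 7 days of intracanal medication, the canal will be accessed under rubber dam isolation". Obturation comes last.

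The Participant timeline says: "Patients will be treated in two visits and will record preoperative and postoperative degree of pain at 6, 12, 24 and 48hrs". It then adds: "Patients will return pain charts to the operator on the second visit".

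The pain chart (Figures 6 and 7) has headings for a training entry, a preoperative entry and one set of readings at 6, 12, 24 and 48 hours. The assessor chart (Figure 8) has one row for each of the same four times.

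**The concern.** The outcome definition starts the clock at the second visit. The working instructions put the readings before that visit. The outcome label does not decide between them, because both visits involve an operation.

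The two windows answer different questions. From 6 to 48 hours after the first visit, the patient has just had instrumentation and the randomised medication is in the canal. From 6 to 48 hours after obturation, the medication has been removed and a further procedure, the same in both arms, has been done. The stated aim is to compare two intracanal medications, so which of these pains is primary defines the estimand.

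At stake is whether the reported primary outcome is the one that was defined. If staff follow the step list and return rule, the data are inter-appointment scores under a definition that says post-obturation. If staff apply the definition literally and keep the return rule, the returned charts lack the primary readings. In either case a reader of the results could not tell from the Protocol which outcome was prespecified.

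**Working it through.** The Protocol gives no figure to reproduce on this point. The check is the order of events, plus simple arithmetic on the clock.

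**Inputs**
- Reading times: 6, 12, 24 and 48 hours (outcome section, procedural steps, Participant timeline).
- Interval between medication and re-entry: 7 days (third-sample step).
- Number of treatment visits: two (Participant timeline).
- Chart return: at the second visit (Participant timeline).
- Planned sample: 36 patients (Sample Size).

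**Step 1: when obturation happens.** Medication is placed at the first visit. The canal is re-entered 7 days later for the third sample, and obturation follows. With only two visits, obturation falls at the second. Its time after medication is 7 × 24 = 168 hours.

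**Step 2: the two windows on one clock.** With hours counted from placement of the medication, a reading at h hours falls at h under a first-visit origin and at 168 + h under the obturation origin.

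| Reading | Origin at medication (inferred from step order) | Origin at obturation (outcome section) |
| --- | --- | --- |
| 6 h | 6 | 174 |
| 12 h | 12 | 180 |
| 24 h | 24 | 192 |
| 48 h | 48 | 216 |

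The last reading under the first-visit origin comes 168 − 48 = 120 hours before obturation, so the windows do not overlap.

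**Step 3: test against the return rule.** A chart handed in at the second visit is handed in at about 168 hours. All four first-visit readings (6 to 48) precede this. All four post-obturation readings (174 to 216) follow it. The return rule therefore fits only the first origin.

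**Step 4: does other text settle it?**
- The minimal clinical differences in Sample Size (3.5 at 24 hours, 4.5 at 48 hours) carry no origin.
- Statistical analysis refers to time periods without an origin.
- The visible headings of the pain chart give no origin. The scales themselves are figures that are not shown, so text inside them cannot be excluded.
- The assessor chart has a date column. Together with visit dates, it might show afterwards what was done, but it does not say what was planned.

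**Step 5: scope.** Four readings in each of 36 patients gives 4 × 36 = 144 planned readings whose timing depends on the answer. The 36 already includes the allowance for losses. The sample-size calculation does not use the time origin, so it is unaffected.

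**The case against.** The strongest reply is that only one origin is actually stated. The step list gives hours without an anchor, so the first-visit origin is an inference. On this view the outcome definition governs and the return rule is the slip. Part of this stands: the step list does not say that the clock starts at placement. But the inference does not rest on step order alone, since the return rule independently needs the readings to be complete before the second visit ends. The reply does not remove the conflict. It shows that the error could lie on either side, so the correction must depend on the sponsor's intent.

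A second reply is that the procedure as written would yield usable data, because the step list and return rule agree with each other. That also stands. The problem is a mismatch between the defined and the collected outcome, not an expected loss of data.

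A reader might infer more than this, in two ways:
- **That readings from both origins would be pooled as one outcome.** The documents do not support this. They provide one chart with one set of readings, one collector (the operator) and one return point. Nothing suggests that some patients would be timed from one visit and some from the other.
- **That the timeline table adds a further contradiction by closing out at 48 hours, before the 7-day sample.** The table has no column for endotoxin samples, obturation or visits, and its last column is follow-up for pain. The row can mean only that pain follow-up closes, which fits either origin.

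**Conclusion.** The point holds as an internal contradiction in the definition of the primary outcome. The outcome section cannot be followed together with the procedural steps and the Participant timeline, and no other text in the Protocol resolves it. The two candidate windows are about 168 hours apart, do not overlap, and measure pain under different conditions. All four primary readings in every patient are affected.

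The conclusion rests on two assumptions: that obturation takes place at the same visit as the third sample, which the two-visit plan implies, and that the interval is close to the stated 7 days. A modest departure from 7 days would not change it.

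The conclusion does not extend to a claim that primary data will be missing. That would follow only if the obturation origin were applied literally while charts were still collected at the second visit.

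**What to change.** Reconcile the outcome section, the procedural steps and the Participant timeline to one stated zero time.

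- **If the sponsor confirms inter-appointment pain:** in the outcome section, replace the reference to the end of obturation with placement of the medication and temporary filling at the first visit. State the same event in the step list and in the chart heading. The step order, the return rule and the question about intracanal medication all fit this choice. The cost is wording only, with no added visit.
- **If the sponsor intends post-obturation pain:** keep the outcome sentence. Move the recording instruction in the step list to after obturation, and replace the return rule with a route for getting charts back after the second visit. The cost is small but real, because the present plan has no contact after that visit at which charts are collected.

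Labelling the 48-hour row of the timeline table as the close of pain follow-up would help but is optional.

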# Research question:

In patients with necrotic teeth and apical periodontitis would the use of antibiotic paste be more effective in reduction of pain and endotoxins than calcium hydroxide or not?

- **Subjects and Methods:**

**1. Setting and location:**

*** Source of patients**: Out patients of the clinic of endodontic at the faculty of oral and dental medicine, Cairo University, Urban area, Cairo governorate.

*** Operator Qualification:** Post Graduate Master’s Degree Student.

*** Dental units**: Adec 200 U.S.A.

* **X-ray machine**: ViVi, S.r.I, Italy.

* **X-ray film**: Intraoral digital sensor.

1. **Eligibility criteria :**
2. *Inclusion criteria:*
   1. Age between 18-55 years old.
   2. Males or Females.
   3. Maxillary or mandibular single rooted premolar teeth with:

- Non-Vital response of pulp tissue.
- Slight widening in lamina dura.
- Tenderness to percussion.
  1. Positive patients’ acceptance for participation in the study.

1. *Exclusion Criteria*:
   1. Pregnant females: Pain degree change may be due to hormonal change, and some medications are contra indicated.
   2. Patients who had received antibiotic treatment during the last 3 months.
   3. Patients having more than one tooth require root canal treatment.
   4. Teeth with:

- Periodontal probing depth > 4mm.

- Could not be isolated with a rubber dam.

- Fluctuant facial swelling (acute abscess)

- Previous root canal treatment.

- **Final Diagnosis:**
- Mandibular or maxillary single rooted premolar teeth with or without pain.
- Tenderness to percussion.
- On using electric pulp tester it gives response of non-vital pulp.
- On radiographic examination it might have slight widening in lamina dura.
- **Intervention:**

Full medical and dental history using a schematic dental chart will be obtained from all patients treated during this study. Each tooth will be evaluated for vitality (sensitivity) of pulp tissues using electric pulp tester

The patients will be randomly divided into 2 groups:

- ***Experimental group***: antibiotic paste intra-canal medication.
- ***Control group:*** calcium hydroxide intra-canal medication.
- **Sequence of Procedural steps:-**

1. Each patient will be given pain scale chart in order to record his /her pain level before any intervention.
2. Tooth will be anaesthetized using nerve block or infiltration technique by local anesthesia^[[1]](#footnote-1)^.
3. Isolation & disinfection:-

Teeth will be isolated with a rubber dam, and disinfection of their external surfaces will be performed by using 30% hydrogen peroxide followed by 2.5% sodium hypochlorite (NaOCl). Subsequently, 5% sodium thiosulfate will be used to inactivate the disinfectant agents.

1. Access:-

A 2-stage access cavity preparation will be performed. The first stage involved the removal of caries without exposure of the pulp chamber by using a high-speed diamond bur. In the second stage, before entering the pulp chamber, the access cavity will be disinfected according to the decontamination protocol described previously. A new bur will be used to access the canal.

1. 1^st^ sample:-

The first endotoxin sample will be taken by introducing the paper points^[[2]](#footnote-2)^ into the full length of the canal (determined by radiographs and apex locator^[[3]](#footnote-3)^) and retaining them in position for 60 seconds. Next, the paper points will be placed in a glass tube and stored at -80^0^C for the LAL assay.

1. Preparation:-

-The root canals will be prepared with Gates-Glidden drills^[[4]](#footnote-4)^ sizes 4, 3 and 2 for the coronal part, and rotary Irace instruments^[[5]](#footnote-5)^ using an endodontic motor^[[6]](#footnote-6)^ with adjusted torque and speed according to the manufacturer's instructions. The rotary files will be introduced inside the canal using EDTA gel^[[7]](#footnote-7)^.

-Before the use of each instrument, irrigation with a syringe (27-G needle) Containing 3ml 2.5% sodium hypochlorite^[[8]](#footnote-8)^.

- Subsequently, 5% sodium thiosulfate will be used to inactivate NaOCl. Then, 5ml saline solution to wash the canal.

1. 2^nd^ sample:-

The second endotoxin sample will be taken as previously described just after the irrigation with saline solution.

1. Intracanal medication:-

The canals will be dried with paper points and filled with intracanal medication plugged into the canal by using Lentulo spiral^[[9]](#footnote-9)^ . The access cavities will be properly filled with Cavit^[[10]](#footnote-10)^.

- **Control group:** Ca (OH)_2_ Paste.
- **Experimental group:** antibiotic paste (ciprofloxacin, metronidazole)

1. The patient will be instructed to record his/her pain level on the pain scale chart after 6 h, 12 h, 24 h and 48 h.
2. 3^rd^ sample:-

After 7 days of intracanal medication, the canal will be accessed under rubber dam isolation by using the protocol for disinfection described previously. The medication will be removed, the final endotoxin sample will be taken just after the irrigation with saline solution.

1. Obturation:-

Root canals will be obturated using lateral condensation technique by proper selection of master cone^[[11]](#footnote-11)^ corresponding to the same size as the master apical file, and then a spreader will be used to allow space for auxillary cones, using resin-based root canal sealer^[[12]](#footnote-12)^

- **Outcomes:**
- **Primary Outcomes:**

The pain scale (0-10 scale) consists of a line anchored by two extremes "No pain" and "the worst pain", patients will be asked to choose the mark that represents their level of pain from 0 to 10, Pain level will be assigned as follow:

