# 0 reading represents “no pain”

# 3 readings represent “mild pain”

# 4- 6 readings represent “moderate pain”

# 7- 10 readings represent “severe pain”

Secondary outcomes will be collected by the operator by commercial standard kit then stored at -80^0^ C so that all samples would be processed at the same time by LAL assay for quantification of bacterial endotoxins.

- **Statistical analysis:**

Data will be analyzed using IBM SPSS advanced statistics (Statistical Package for Social Sciences), version 21 (SPSS Inc., Chicago, IL). The level of endotoxins will be described as mean and standard deviation. The level of pain will be described as median and range or interquartile range, as appropriate. The level of endotoxins will be explored for normality using Kolmogrov-Smirnov test and Shapiro-Wilk test. If the exploration of data reveals that the collected values are normally distributed, a 2-way ANOVA with repeated measures will be performed to compare between the 2 groups and the change with time. If the interaction between the groups and time is found to be significant, a 1-way repeated measures ANOVA will be used to examine significant differences between time periods within each of the two groups. The Student’s t-test will be performed to test the significance between the two groups at each time period. If the exploration of data reveals that the level of endotoxins is not normally distributed and for the analyses of the pain score, Mann-Whitney U test will be performed to test the significance between the 2 groups at each time period. Friedman’s test followed by multiple comparisons test will be performed to test the significance between the 4 time periods within each group. In addition, correction of p-value will be done using Bonferroni adjustment to avoid hyperinflation of type 1 error that arises from multiple comparisons. A p-value less than or equal to 0.05 will be considered statistically significant. All tests will be two tailed. The effect size will be measured using standardized mean difference.

- **Data monitoring:**

There will not be a Data Monitoring Committee for the following reasons:

- Interim analysis is not involved in the trial so periodic inspection of the accumulating outcome data is not required.
- Short duration of the trial.
- Minimal risks of the trial.
- **Harms**

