Adverse events are minimal or rare. However, if any harm is seen in the participants either in intervention or control groups they will be recorded and reported at the end of the trial. It will be documented as part of routine monitoring not as outcome. The treatment will be according to the harm:

- Pain: administration of Analgesics.
- Swelling: hot fomentation, mouth rinse with salty warm water, antibiotic will be administrated.
- Allergic reaction: referral for a physician for corticosteroid therapy.
- Auditing

In this trial, auditing will be performed in order to preserve the integrity of the trial, the audit will review the processes of participant enrolment, consent, eligibility, allocation to study groups and adherence to trial interventions and policies to protect participants.

- **Ethics and dissemination**
- **Research ethics approval:**
- This protocol and the template informed consent form will be reviewed by the Ethics Committee of Scientific Research, faculty of oral and dental medicine, Cairo University.
- Each of the protocol, informed consent forms in Arabic and English language, recruitment materials and any modifications will be done later on also will be reviewed and approved by the ethical review Committee.
- **Protocol amendments:**

The ethical committees will notified any administrative changes or modifications of the protocol or modification of registered online protocol.

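### The eligibility criteria do not exclude known hypersensitivity to the two antibiotics in the experimental paste, although the protocol foresees allergic reaction as a possible harm

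*Protocol*

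**What the plan says.** The Exclusion Criteria in the protocol contain three patient-level entries:

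- "Pregnant females: Pain degree change may be due to hormonal change, and some medications are contra indicated"
- "Patients who had received antibiotic treatment during the last 3 months"
- "Patients having more than one tooth require root canal treatment"

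A fourth entry lists tooth-level conditions: probing depth above 4 mm, "Could not be isolated with a rubber dam", fluctuant facial swelling, and earlier root canal treatment. The Inclusion Criteria cover age, sex, tooth type with its findings, and willingness to take part.

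Under Intervention the protocol adds: "Full medical and dental history using a schematic dental chart will be obtained from all patients treated during this study". The Intracanal medication step gives the experimental product as "antibiotic paste (ciprofloxacin, metronidazole"), and the third-sample step shows that the medication stays in place for 7 days. Under Allocation concealment mechanism, patients draw an envelope, and after instrumentation the operator opens it and applies whatever it assigns.

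The Harms section describes adverse events as few or uncommon, then says how three kinds would be handled: pain, swelling, and a third entry, "Allergic reaction: referral for a physician for corticosteroid therapy".

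**The concern.** The protocol accepts in one place that a contraindicated medicine is a reason to keep a patient out, but applies that reason to pregnancy only. It foresees allergic reaction well enough to plan a response. Its experimental product consists of two antibiotics. Yet its entry criteria do not ask whether the patient is already known to react to either drug.

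What is at stake is an avoidable exposure. An operator who follows the criteria as written would enrol a patient reporting such an allergy, and the envelope could assign the paste. Participants are blinded to their group, so the patient could not be relied on to object when the paste is placed.

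**Working it through.** No arithmetic on power or error rates applies. The check is to read every criterion and then every later step at which an allergy could be caught.

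**1. The criteria.** There are 4 inclusion entries, 3 patient-level exclusions and 4 tooth-level exclusions, so 4 + 3 + 4 = 11 items. Of these, 0 mention allergy or hypersensitivity. The two nearest do not cover it:

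- The antibiotic exclusion concerns use in the preceding 3 months. A patient with a long-standing allergy who has avoided the drug passes it.
- The remark about contraindicated medication is the reason given for excluding pregnancy. It is not a criterion in its own right.

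**2. The later steps.**

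| Place in the protocol | What it provides | Does a known allergy have a stated consequence? |
| --- | --- | --- |
| Intervention | Full medical and dental history from all patients | No |
| Baseline data collection | A general health chart (figures not shown) | No; described as data collection |
| Intracanal medication | Ciprofloxacin and metronidazole paste in the experimental arm | No |
| Allocation concealment mechanism | Envelope opened after instrumentation, assigned medication used | No check at this step |
| Harms | Response to an allergic reaction once it has occurred | No; acts after exposure |

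**3. Reading them together.** The only readable mention of allergy is the entry under Harms, which applies once a reaction has happened. The history is described ahead of the procedural steps, so the information would normally be in hand before the assignment is seen. What is missing is a rule that acts on it. Literal application of the criteria therefore admits a patient with a known allergy to a component of the paste.

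**The case against.** The strongest reply is that this is ordinary clinical care. A dentist who takes a full medical history will ask about drug allergy and will not place a drug to which the patient is known to react. The general health chart and the consent form are not shown and may contain the question. This much stands: the documents do not show that allergy goes unasked, and a careful operator may well act on it. But a question on a chart is not an eligibility rule, and the written criteria, which are complete in the text, attach no consequence to the answer.

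A reader might infer four stronger points, and the documents do not support them.

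- *That the protocol expects allergic reactions to the paste.* It does not. The Harms section treats adverse events as uncommon, and its list covers harm in either group without attributing any entry to the paste. It foresees the possibility, no more.
- *That the comparison is biased.* If an allergy to one of the two antibiotics were acted on only after the envelope was opened, the resulting loss would fall in the paste arm alone. But the history comes before the envelope is opened, so late discovery is possible without being the expected path. One such loss would be 1/18 = 5.6% of the arm, against a planned allowance for losses of around 25%. That allowance does not cure a one-sided loss, but it shows how small this one would be. For the anaesthetic and other materials used in both arms, the loss would not be one-sided at all.
- *That the likely number of affected patients can be calculated.* The documents give no prevalence of hypersensitivity to either drug, so any figure would rest on an unsupported rate.
- *That "Minimal risks of the trial", one of three reasons given for having no monitoring committee, is contradicted.* Such a committee reviews accumulating data and does not screen patients at entry. The omission does not bear on that decision.

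**Conclusion.** The point holds as a gap in the eligibility criteria and should be fixed on the ground of participant safety. As written, a patient with known hypersensitivity to ciprofloxacin or metronidazole is eligible and can be assigned the paste, while the same protocol foresees allergic reaction and already collects the history that would identify such a patient. Eligibility belongs in the protocol, so this is not something left to a statistical analysis plan.

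Its size cannot be put as a number from the documents, and the conclusion does not need one. It changes no sample size, error rate or analysis. Its only statistical side is modest: screening before allocation avoids a possible post-allocation loss confined to the paste arm.

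The conclusion rests on the criteria being applied as written, and on the charts and consent form that are not shown not containing an eligibility rule absent from the protocol's own list.

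**What to change.** Reconcile the eligibility list with the Harms section by adding known hypersensitivity to the study medicaments to the Exclusion Criteria. State that it is checked in the medical history already taken and before the envelope is drawn. The exact wording, including how far it extends to related drugs, is for the investigator to settle.

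The cost is one line in the criteria and one check on an existing form. The downside is possibly one fewer eligible patient. Nothing in the treatment, the allocation ratio or the analysis needs to change.
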